### Data management, quality assurance, and ethical considerations

Data use agreements (DUAs) have been executed between relevant institutions so that investigators can share data related to implementation outcomes. Using an honest broker at each CHC, we have established a process to de-identify datasets, including transformation of dates of service and assignment of unique study identification codes (IDs) for patients. The business associate agreements (BAAs) and DUAs that have been executed between the partners involved in this study do not allow for the publication of anonymized data. Data sets will contain both individual-level data, including some limited health information that cannot be anonymized, and aggregate data. Thus, the data sets cannot be made publicly available.

Only minimally necessary data will be collected in both the pre-implementation and implementation phases. All data will be stored on secure servers at the University of Chicago. Only individuals with IRB approval and a record of human subject research training will have access to data during this study. Data will be stored until all dissemination activities for this study have been completed. Data will be transmitted to the University of Chicago using secure encrypted channels. Any data sent from the University of Chicago to other institutions will be de-identified.

We will establish a Data Safety Monitoring Board (DSMB) to protect the safety of study subjects and assure the quality of the research data generated is acceptable. The DSMB will consist of one chair and four members at the University of Chicago, Northwestern University, and other peer institutions. The Chair will convene the DSMB semi-annually for the duration of the program’s implementation to monitor data acquisition (accuracy, timeliness, and completeness) and issues related to participant safety and confidentiality, as well as to assess the progress of the study and the quality of data management and analysis. We will employ established procedures for adverse event (AE) reporting at the University of Chicago. The DSMB will have access to interim analyses/results and provide input on stopping guidelines.

This study is approved by the University of Chicago Institutional Review Board (IRB 21–0971). All organizations that are considered engaged in research for this study have agreed to rely on the IRB at the University of Chicago. Informed verbal consent will be obtained from participants for the pre-implementation focus groups and for the quantitative surveys and the individual interviews conducted as part of evaluating the implementation of POWER Up. The extraction of patient data from the EMR during the implementation period is considered part of routine care and does not require explicit consent from participants. DUAs and BAAs have been executed between institutions for the sharing of safe harbor and limited datasets for patients.

### Modifications to protocol

The team will continue to modify the protocol as needed to strengthen the study design and facilitate implementation and evaluation of the POWER Up strategies at each participating site. All proposed changes will be discussed with implementation partners and key stakeholders and will be approved by the University of Chicago IRB prior to application. Notification of amendment approvals and subsequent protocol modifications will be disseminated to the appropriate parties.

### Analysis

#### Qualitative data

For focus groups and individual interviews conducted during the pre-implementation, implementation, and post-implementation phases of the study, rapid qualitative analysis (RQA) and thematic coding will be utilized [38–40]. The research team will create a codebook with unique definitions for each code based on the CFIR [28], and Dedoose software will be used for analysis [41]. During the pre-implementation phase, qualitative data will be utilized to inform the adaptation of the POWER Up strategies, taking specific clinic and contextual factors into consideration.

During the implementation and post-implementation phases, we will conduct individual interviews with providers and patients. We will assess the process of implementing the POWER Up strategies and gather feedback on the strengths and weaknesses of the implementation via interview guides based on the CFIR. We will analyze these data using Dedoose to elicit key themes that will inform how we improve the process of implementing the bundle of POWER Up strategies at other sites nationwide. Additionally, we will document how the POWER Up strategies are adapted and modified at each clinic during the implementation process using the Framework for Reporting Adaptations and Modifications to Evidence-based Implementation Strategies (FRAME-IS) [42]. These findings will be included in our dissemination guide to help illustrate significant processes and mechanisms by which the bundle of POWER Up strategies exerted its effects.

#### Quantitative data

For EMR variables, we will use descriptive statistics to examine the distribution of the data. We will compare the distribution of patient characteristics between the unexposed observations from the control period and the exposed observations during the implementation period. Outcome rates will be plotted over each six-month time period, comparing how rates differ from the control period to the implementation period between CHCs within a geographic area (Midwest or South), as well as within each CHC, to examine the effects of the implementation site and calendar time on outcomes. Additionally, rates will be compared by geographic area to detect differences in implementation effect size between the Midwestern and the Southern sites. We will use an intention-to-treat analysis to ensure that if a CHC deviates from the assigned implementation timeline (i.e., they begin the implementation of the bundle of POWER Up strategies earlier or later than planned), the most conservative estimate of the size of the implementation is used. To examine treatment effects for the effectiveness and individual maintenance outcome related to PrEP uptake (initial prescriptions and refills), we will use a generalized linear mixed model, with a random effect for each CHC and a random effect of time per CHC [35, 43–45].

For RE-AIM outcomes, we will first use descriptive statistics to examine the distribution of the data. Bivariate analysis will be employed to explore differences between groups (e.g., differences between clinics or time points). Fisher’s exact test and chi-square tests (for categorical variables) and t-tests (for continuous variables) will be used to identify factors correlated with RE-AIM outcomes. All statistical analyses will use two-tail alpha to reject null hypotheses at 0.05. To measure associations of various factors with RE-AIM outcomes, we will report odds ratios along with 95% confidence intervals. Statistical assumptions such as data normality will be confirmed, or data transformations or alternate non-parametric methods that do not break model assumptions will be used. We anticipate nominal missing data, but we are willing to consider methods such as multiple imputation if needed to preserve sample size.

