### Implementation of POWER Up

To improve PrEP uptake and persistence among Black women, multifaceted and multi-level strategies must target each step of the PrEP care continuum (i.e., awareness of PrEP, identification of PrEP-eligible candidates, prescription and initiation of PrEP, persistence of care during HIV risk periods, and re-initiation of care following discontinuance) [10]. Through preliminary work, our team has identified successful strategies for improving PrEP care continuum outcomes among Black women. We performed formative research guided by the Consolidated Framework for Implementation Research (CFIR 2.0) [28], including mixed methods studies of client-, health system-, and provider-level barriers and facilitators to PrEP initiation and persistence among Black women [11, 29–33]. Through this work, we have identified a set of five strategies that have been successful in community health clinic (CHC) settings for PrEP Optimization among Women to Enhance Retention and Uptake (POWER Up). POWER Up strategies include 1) routine PrEP education to raise awareness of PrEP among Black women; 2) standardized provider training for how to identify women who are PrEP candidates, discuss HIV risk and teach women about PrEP, and prescribe PrEP and engage them in PrEP care; 3) electronic medical record (EMR) tools for identifying women who would benefit from PrEP, prescribing PrEP, and tracking PrEP outcomes; 4) PrEP navigation to assist with PrEP initiation and persistence; and 5) clinical champions for supporting the successful creation and implementation of PrEP-related processes (Fig 1). With these POWER Up strategies, a CHC in the Midwest has more than doubled the rate of PrEP uptake among Black women and maintained PrEP persistence rates above the national average (mean persistence among ciswomen of 8.1 months vs. 5.8 months nationally) [7, 29]. Our study will implement this bundle of strategies in 3 CHC networks (1 in the Midwest and 2 in the South), with the goal of increasing PrEP uptake and persistence among Black women.

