## Materials and methods

### Aims and objectives

The aim of this study is to assess the acceptability and feasibility of implementing POWER Up as part of routine care in CHC settings and to assess the adaptation and efficacy of the implementation strategy package as it is implemented by comparing pre- and post-implementation rates of PrEP prescription among Black women at each CHC. The project has three specific aims. Aim 1 is to undertake qualitative data collection through provider and patient focus group discussions (FGDs) to inform the adaptation and implementation of POWER Up strategies for engaging Black women in the PrEP care continuum for use in CHCs. Aim 2 is to measure the implementation and effectiveness outcomes of the adapted bundle of implementation strategies in the Southern United States compared to the approach in the Midwest. This aim will be accomplished via a stepped-wedge cluster randomized trial (SW-CRT) to measure change in implementation outcomes and evaluation using the Reach, Effectiveness, Adoption, Implementation, and Maintenance (RE-AIM) framework. We will implement the POWER Up strategies across diverse geographic areas and assess the change in clinical and implementation outcomes from the pre-implementation (control) and the post-implementation (implementation) periods. The cluster, or unit of analysis, is each CHC, N = 12 (8 in the South, 4 in the Midwest). Aim 3 is to develop an implementation guide that can be utilized across U.S. jurisdictions to improve PrEP care continuum engagement among Black women, reflecting the knowledge gained through the adaptation and evaluation processes.

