### Settings

POWER Up is being rolled out sequentially in 12 CHCs among 3 health networks in the Southern and Midwestern United States: Advance Community Health (North Carolina), Evara Heath (Pinellas County, Florida) and Erie Family Health Centers (Cook County, Illinois). Two of the health networks are located within priority jurisdictions of the CDC’s Ending the HIV Epidemic (EHE) initiative based on the high burden of HIV infection (Pinellas County, FL and Cook County, IL) [34]. These networks were selected due to their area’s elevated incidence of HIV, as well as the high volume of PrEP-eligible Black women who receive care at their sites. POWER Up has not been replicated elsewhere, so it is important to consider geographic location as a factor in implementation success. Although the goal of this project is to improve PrEP care continuum outcomes among Black women in the South, we are also including Midwestern sites to serve as a comparison in effectiveness to Southern sites. We chose to include different geographic regions so that the dissemination guide is relevant nationally to increase the likelihood that POWER Up strategies are able to be implemented nationwide. All participating CHCs currently have very low PrEP usage among Black women (less than 1%) who receive care at their sites, and none of the CHC sites have previously implemented the bundle of POWER Up strategies.

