### Study design

We will utilize a SW-CRT to measure change in our primary implementation outcome, PrEP uptake. This study design will allow us to roll out the bundle of implementation strategies across diverse geographic areas and to assess the change in clinical and implementation outcomes from the pre-implementation (control) and the post-implementation (implementation) periods. There will be 12 clusters: 8 CHCs in the South and 4 CHCs in the Midwest (N = 12). In a stepped-wedge study, each clinic contributes both time and observations to the control condition (usual care) and the implementation condition (implementation of POWER Up strategies). Every clinic switches from the control to the implementation at regular time intervals (steps), but at different points in calendar time depending on randomization order [35]. Additionally, more than one clinic may start the bundle of POWER Up implementation strategies at a step. The design uses repeated cross-sectional collection of data, with our primary outcome obtained from patients seen during each time period (each step) at each clinic rather than following individually recruited patients over time. For our two PrEP persistence measures, patients are followed longitudinally after starting PrEP. This is a robust design because each clinic provides data under both the control and implementation conditions, reducing variability between the two conditions and improving precision when intra-cluster correlation is high, which is likely among the CHCs that we have chosen. As stepped-wedge designs consist of a unidirectional move from control to implementation, the bundle of POWER Up strategies is not withdrawn once implemented, alleviating ethical concerns [36].

In our stepped-wedge design, each step is 6 months long, and there are 4 waves of implementation (Fig 2). Three CHC sites will be randomized to each step, with a mix of sites from the South and the Midwest included. Each cluster also undergoes a 6-month transition period when the individual clinics will prepare to implement the bundle of POWER Up strategies. The sequence of switching from control to implementation condition at each site (each cluster) will be determined using a computer-based list randomization application to create 4 waves of implementation (three sites begin the implementation at the same step, a mix from the South and the Midwest).

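### The Aim 2 South-Midwest difference in effect is to be detected by comparing rates by area, on no stated scale and outside the mixed model, and it cannot be credited to geography because one network is the whole Midwest

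*Protocol article*

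**What the plan says.** The regional contrast is a declared purpose of the trial. Under Aims and objectives, Aim 2 is to measure outcomes of the "adapted bundle of implementation strategies in the Southern United States compared to the approach in the Midwest". Under Settings, the article explains that "we are also including Midwestern sites to serve as a comparison in effectiveness to Southern sites".

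The method is in Analysis, Quantitative data. Outcome rates are first plotted by six-month period, "comparing how rates differ from the control period to the implementation period between CHCs within a geographic area (Midwest or South") and within each clinic. The article then adds that "rates will be compared by geographic area to detect differences in implementation effect size between the Midwestern and the Southern sites". Separately, for treatment effects on uptake and individual maintenance, "we will use a generalized linear mixed model, with a random effect for each CHC and a random effect of time per CHC". The regional sentence names no effect measure and does not refer to this model.

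Two design facts matter. The clusters are "8 CHCs in the South and 4 CHCs in the Midwest (N = 12"), and they belong to "3 CHC networks (1 in the Midwest and 2 in the South"). For allocation, "Three CHC sites will be randomized to each step, with a mix of sites from the South and the Midwest included". Settings also says that PrEP use among Black women is below 1% at every clinic, with no figure by region.

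**The concern.** A rate is not an effect. Whether the bundle works better in one region than in the other is a question about an interaction, and its answer depends on the scale. With outcomes this rare, two regions that share the same relative effect but start from different baselines will show different absolute rates and different absolute changes. If the scale is chosen once the rates are known, either answer may be available.

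The second difficulty lies in the design. All four Midwestern clinics belong to one network in Illinois. Whatever is particular to that network (its record system, leadership or local policy) is indistinguishable from being in the Midwest.

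At stake is the Aim 2 conclusion and, through it, the implementation guide, which Settings wants to be relevant nationally. A difference that reflects baseline use, a local trend or one network could be passed on as a finding about geography.

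**Working it through.** The article gives no power figure, intracluster correlation or regional target, so there is no stated result to reproduce beyond the cluster count: 4 waves × 3 clinics = 12 = 8 + 4, which agrees. Baselines, odds ratios (OR), trends, correlations, clinic sizes and between-network spread below are assumptions.

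**1. Scale.** Assume baselines of 0.9% (Midwest) and 0.2% (South), a common OR of 3 and no trend. The implementation rate is 3o/(1 + 3o), where o is the baseline odds.
- Midwest: o = 0.009/0.991 = 0.00908, giving 2.65%.
- South: o = 0.002/0.998 = 0.00200, giving 0.60%.
- Difference in implementation rates, South minus Midwest: 0.598 − 2.652 = −2.05 points.
- Difference in change: (0.598 − 0.2) − (2.652 − 0.9) = −1.35 points.
- Ratio of ORs: 3/3 = 1.00.

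A milder case, 0.6% against 0.4% with a common trend of OR 1.15 per period, gives −1.01 points on rates and −0.78 on changes, with the ratio of ORs still 1.00.

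**2. Calendar time.** Four Midwestern clinics spread over four waves, each holding both regions, allow only 1 Midwestern + 2 Southern per wave. Take six half-year periods from January 2023 to December 2025, transition cells left out and clinics of equal size. Control cells then have mean period (4×1 + 3×2 + 2×3 + 1×4)/10 = 2.0, and implementation cells (1×3 + 2×4 + 3×5 + 4×6)/10 = 5.0, in both regions.
- Common trend, OR 1.15 per period, baseline 0.5%, true OR 3: the crude before-after OR rises to 4.56 in both regions, so the ratio of ORs stays 1.00.
- Flat Midwest, 1.15 per period in the South: crude ORs are 3.00 and 4.56, a false ratio of 4.56/3.00 = 1.52.

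**3. Region and network.** Consider four model columns: implementation, implementation × South, and implementation × each Southern network. The last two add up to the second, so the rank is 3 of 4. Three network effects can be estimated, but not a region effect as well as network effects. If log-ORs vary between networks with standard deviation τ, the region contrast has a standard error of at least τ√(1/1 + 1/2), however many patients are seen: 0.12, 0.24 and 0.37 for τ = 0.1, 0.2 and 0.3. If the within-network standard error were 0.2 and τ = 0.2 were ignored, the true standard error would be √(0.04 + 0.06) = 0.316. The critical value would shrink to 1.96 × 0.2/0.316 = 1.24, a type I error of about 21% rather than 5%.

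**4. Precision of a proper interaction.** I used generalised least squares for this layout, with intracluster correlation 0.01 to 0.10, cluster autocorrelation 0.8 to 1.0 and 20 to 250 patients per clinic-period.
- Common period effects: the interaction variance is 0.97 to 1.12 times that of the overall effect.
- Region-specific period effects: the regions are estimated separately from 4 and 8 of the 12 clinics, so the ratio is 12/4 + 12/8 = 4.5. If the overall effect has 80% power, an interaction of the same size has Φ((1.96 + 0.84)/√4.5 − 1.96) = Φ(−0.64), about 26%.

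**The case against.** Four points can be made for the plan, and each stands in part.

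- **Raw rates.** A reader might infer that raw rates will be set side by side. The sentence before points to control-to-implementation changes, and the regional sentence names effect size as its object. That is the fairer reading. It does not settle the matter, because absolute changes also differ under an identical OR (1.35 points above). One may reply that a larger absolute rise is a genuinely larger effect on that scale. That is true, and it is why the scale has to be fixed.
- **Calendar time.** A reader might infer that the contrast is confounded with secular trend in general. The documents do not support this: the mixed waves give both regions the same calendar distribution, so a common trend cancels if clinic sizes are similar. Only trends that differ by region, or unequal clinic sizes, leave a problem, and the article shows neither.
- **The model.** A reader might infer that the mixed model wrongly omits region. The article lists no fixed effects at all, not even implementation, and full specification may sit in the statistical analysis plan. The point therefore rests on the rate comparison that is stated, not on a missing term.
- **One Midwestern network.** This is openly disclosed and cannot be cured by analysis. No regional hypothesis or target is stated, and the comparison sits with the descriptive work. Yet the article includes the Midwestern sites as an effectiveness comparator, speaks of detecting a difference, and nowhere limits the interpretation.

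**Conclusion.** The point holds in limited form. The stated method does not identify the quantity Aim 2 asks for: it compares rates on an open scale, with no link to the model that estimates the effect. Under the assumed baselines, an identical OR appears as a 1.35-point regional difference in change. Under an assumed trend confined to the South, it appears as a crude ratio of ORs of 1.52. Both are illustrations, since the article gives no regional baselines or trends. The confounding of region with network needs no assumption: it follows from one Midwestern network against two Southern ones. Its inferential cost depends on τ, which is unknown.

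A reader might go further and infer that the trial's main result is compromised. It is not. The overall effect on uptake does not depend on this contrast. What must change is how the contrast is estimated and what may be concluded from it.

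**What to change.** Replace the rate comparison with a defined contrast:

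1. Estimate a region-by-implementation interaction in the planned mixed model, on a stated scale such as the odds ratio, adjusted for period. Include region as a fixed effect, because allocation was restricted on it.
2. Add region-specific period effects as a sensitivity analysis.
3. Report the three network-specific effects with confidence intervals.
4. Label the contrast exploratory, describe it as one Illinois network against two Southern networks, and state in the results and the implementation guide that it is not attributable to geography.

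The change is to analysis wording, with no new data. Its price is a more modest Aim 2 claim and an imprecise estimate: in the sensitivity analysis the variance is about 4.5 times that of the overall effect, and any variation between networks comes on top. The version with common period effects is much more precise but assumes that the regions share a trend, so the two should be read together. None of this separates region from network, which would take more than one Midwestern network.

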We will collect both patient-level and clinic-level data from each CHC on a monthly basis. These data will be collected in two ways: 1) by the aggregation of data from patient-level EMR records and 2) by surveys among patients and providers designed to measure knowledge, beliefs, and satisfaction regarding PrEP and the implementation strategies. All EMR data will be collected during each of the three phases of the stepped-wedge trial: 1) pre-implementation; 2) transition, and 3) implementation phases. Table 1 shows the list of EMR variables that will be collected from each site on a monthly basis during the stepped-wedge trial. To obtain these EMR variables, we will aggregate data from individual patient records (~3,000) that meet each variable definition. No recruitment of patients is required for the monthly EMR data collection, as POWER Up is considered part of routine care. The survey data that will be collected vary in the stages of the stepped-wedge trial and the frequency of assessment. Some of these measures will be collected and evaluated monthly, and some will be collected once for pre- and post-implementation (i.e., pre-implementation and at the end of the implementation period). Clinical champions at each site will assist with monitoring adherence to implementation protocols at each site. Table 2 shows outcomes that will be collected via quantitative surveys and qualitative interviews based on the RE-AIM framework [37] and their associated time periods of collection. These surveys and interview guides will be composed of previously validated questions whenever possible and include CFIR domains to assess implementation success. CHC providers and patients will be recruited to complete these quantitative surveys and qualitative interviews via the same recruitment methods used for pre-implementation focus groups (e.g., provider recruitment emails and routine phone calls/recruitment flyers for patients).

**Table 2 pone.0285858.t002:** Data collected for evaluation of implementation using the RE-AIM framework.

Data Variable	Time Collected from Healthcare Network	Brief Description & Source of Data	RE-AIM Dimension
Change in provider knowledge and attitudes about PrEP	Once during control period (baseline) and once at end of implementation period	Average change in score between baseline and post implementation survey about provider knowledge and attitudes about PrEP; qualitative interview	Effectiveness

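### The tests named for RE-AIM outcomes outside the mixed model do not adjust for clustering in 12 clinics, so clinic-level and control-versus-implementation contrasts can look too precise

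*Protocol article*

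**What the plan says.** All of the method text is in the protocol article, under Analysis, Quantitative data.

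- The first paragraph gives a generalized linear mixed model with a random effect for each CHC and a random effect of time per CHC. It is limited to the effectiveness and individual maintenance outcomes related to PrEP uptake.
- The second paragraph covers RE-AIM outcomes. Its bivariate step is meant to "explore differences between groups (e.g., differences between clinics or time points". The tools are Fisher's "exact test and chi-square tests (for categorical variables) and t-tests (for continuous variables) will be used to identify factors correlated with RE-AIM outcomes".
- On error control: "All statistical analyses will use two-tail alpha to reject null hypotheses at 0.05".
- On estimation: "we will report odds ratios along with 95% confidence intervals".

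That paragraph mentions no clinic term, robust variance or clinic-level summary. Its sentence on checking assumptions gives normality as the example, with transformations or non-parametric methods as the remedy. Neither deals with clustering.

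Elsewhere the article treats clustering as central. Aims and objectives: "The cluster, or unit of analysis, is each CHC, N = 12 (8 in the South, 4 in the Midwest". Study design, on the advantage of the stepped wedge: "improving precision when intra-cluster correlation is high, which is likely among the CHCs that we have chosen".

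**The concern.** Chi-square, Fisher and two-sample t-tests assume independent observations. Patients and providers in one clinic share workflow, staff and population, and the article itself expects them to be correlated. A test that ignores this counts every record as new information, so its standard error is too small wherever the contrast runs partly or wholly between clinics.

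Two kinds of contrast are exposed. One is a clinic-level factor, such as South against Midwest. The other is a pooled comparison of control with implementation records for the reach measures in Table 1 (risk assessment, education, offer). In a stepped wedge the second contrast also sets earlier against later calendar time, and the named tests have no period term.

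The primary outcome is not at stake. What is at stake is the secondary evidence on reach, adoption and acceptability, which feeds the Aim 3 implementation guide.

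**Working it through.** The article states no sample size, power or intra-cluster correlation (ICC), so there is no figure of its own to reproduce. The check asks how far a nominal 5% test can drift under assumed inputs.

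**Inputs from the article.** Two-sided alpha 0.05; 12 clinics (8 South, 4 Midwest); 4 waves of 3 clinics; 6-month steps; one 6-month transition per clinic. The only volume figure is "we will aggregate data from individual patient records (~3,000) that meet each variable definition", with no statement whether this is per month, per site or in total.

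**Assumptions.** ICC 0.01 to 0.10; a 30% outcome; six 6-month periods with one wave moving at each step; equal numbers per cell.

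**Step 1: clinic-level factor.** With m people per clinic, the design effect is DE = 1 + (m − 1) × ICC, and the real error is 2 × [1 − Φ(1.96/√DE)].

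| m per clinic | ICC | DE | Real error |
|---|---|---|---|
| 10 | 0.05 | 1.45 | 10.4% |
| 10 | 0.10 | 1.90 | 15.5% |
| 50 | 0.05 | 3.45 | 29.1% |
| 250 | 0.01 | 3.49 | 29.4% |
| 250 | 0.05 | 13.45 | 59.3% |

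Simulated chi-square tests of 8 against 4 clinics agree: 10.2% (m = 10, ICC 0.05), 28.8% (m = 250, ICC 0.01) and 58.7% (m = 250, ICC 0.05).

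**Step 2: pooled control versus implementation.** A wave-k clinic has k control periods and 5 − k implementation periods. Control cells: 3 × (1+2+3+4) = 30. Implementation cells: 3 × (4+3+2+1) = 30. If the roughly 3,000 records are a total, that is 3,000/60 = 50 per cell; 250 per cell would need 15,000.

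Clinics do not cancel in this contrast. The net weight per clinic is (5 − 2k)/30, that is 3/30, 1/30, −1/30 and −3/30 by wave. The squared weights sum to 3 × (9+1+1+9)/900 = 1/15. The naive variance is p(1 − p) × 2/(30m). The ratio of true to naive variance is therefore (1 − ICC) + (1/15) × 15m × ICC = 1 + (m − 1) × ICC, even when clinic effects are perfectly stable over time. Here m is per clinic-period.

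A clinic SD on the logit converts approximately as ICC ≈ SD² × p(1 − p): 0.04 × 0.21 = 0.0084 for SD 0.2, and 0.25 × 0.21 = 0.0525 for SD 0.5. The formula then gives:

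- SD 0.2: DE 1.08, 1.41 and 3.09 at m = 10, 50 and 250; real error about 6%, 10% and 27%.
- SD 0.5: DE 3.57 and 14.07 at m = 50 and 250; real error about 30% and 60%.

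Simulated false-positive rates of the chi-square test, with no effect and no trend:

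| Clinic SD, clinic-by-period SD | 10 per cell | 50 per cell | 250 per cell |
|---|---|---|---|
| 0.2, 0 | about 5–7% | 9% | 27% |
| 0.25, 0.1 | about 6–7% | 13% | not tabulated |
| 0.5, 0 | not tabulated | 29% | 59% |
| 0.5, 0.3 | not tabulated | 34% | 63% |

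Without clustering the rate is about 5–6%, so the excess comes from clustering.

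**Step 3: calendar time.** With clinic SD 0.5 and a secular trend of odds ratio 1.1 per period, but no intervention effect, the same test rejects in 81% (50 per cell) and 94% (250 per cell) of simulated trials.

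**Step 4: where the tests are about right.** For an individual-level factor balanced within clinics, simulated error is 4.9–5.5%. For a comparison once before and once after, with equal numbers in the same clinics and perfectly stable clinic effects, DE = 1 + (m − 1) × ICC − m × ICC = 1 − ICC. At ICC 0.05 this gives 4.4%, slightly conservative. If the correlation of clinic effects between the two times is 0.8, the error is 6.8% at m = 20 and 29.1% at m = 250.

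**The case against.** **Scope.** The two analysis paragraphs open with EMR variables and RE-AIM outcomes respectively, so the second could be meant only for the surveys in Table 2. On that reading the 50- and 250-per-cell figures fall away, and the 10–16% for ten providers per clinic is the relevant size. The text does not settle this: Table 1 also assigns every EMR variable a RE-AIM dimension. The reach figures therefore hold only on the broader reading. The missing adjustment holds on both.

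**Exploratory use and condensation.** The bivariate step is described as exploring, and an article may leave modelling detail, including the model behind the odds ratios, to a fuller plan. That is fair for the odds ratios, where the point is only that no adjustment is named. It does not cover the tests, which are named together with a 0.05 rejection rule.

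**Stronger readings that the article does not support.**

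- A reader might infer that all RE-AIM inference is badly wrong. Uptake and related persistence go to the mixed model, factors balanced within clinics are near nominal, and a contrast among the 12 named clinics taken as fixed is not inflated.
- A reader might take 63% as the expected error. It needs 250 records per clinic-period and large clinic variation, neither of which is stated.
- A reader might say that paired survey data will be analysed as unpaired. Nothing says the same people answer both surveys, and the word t-tests does not exclude paired ones.
- A reader might apply the calendar-time point to the acceptability, appropriateness, feasibility and sustainability scores. These are collected once, at the end, so they have no time contrast.

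**Conclusion.** The concern holds in limited form. For RE-AIM outcomes outside the uptake and persistence model, the stated tests make no allowance for clinic, which conflicts with the article's own unit of analysis and its expectation of high intra-cluster correlation. Clinic-level factors and pooled control-versus-implementation contrasts of reach are affected, and the latter are also confounded with calendar time.

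The size is a range, not an estimate. For the pooled contrast, real error runs from close to nominal with few patients per cell and little clinic variation, through roughly one in ten to one in three at 50 per clinic-period, to well over half at 250 with large clinic variation. These figures assume six periods, a 30% outcome, equal cells and clinic SDs of 0.2 to 0.5 on the logit. The survey figure assumes ten providers per clinic and ICC 0.05 to 0.10.

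**What to change.** - **Patient-level reach outcomes:** analyse with the mixed model already planned for uptake (CHC and CHC-by-time random effects). Add fixed period effects, which the article does not name, and a small-sample correction for 12 clusters.
- **Survey outcomes:** use a model with a CHC random intercept, or a clinic-level analysis. Add a person effect only if respondents can be linked across the two surveys.
- **Odds ratios and intervals:** take them from these models.
- **Unadjusted chi-square, Fisher and t-tests:** treat as descriptive.
- **Scope:** state which outcomes in Tables 1 and 2 the RE-AIM paragraph governs.

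The cost is a change of wording and modest programming, with no new data. Intervals will widen for the affected contrasts: for a clinic-level factor the standard error grows by √DE, for example √1.45 = 1.20 with 10 per clinic and √3.45 = 1.86 with 50 per clinic, both at ICC 0.05.
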